#### Control group—large-volume paracentesis

Ultrasound-guided (Ultrasound GE Vivid T8®) placement of an intra-abdominal catheter, 14 Gauge Optiva®, or similar, as indicated by the attending physician in accordance with international clinical guidelines [1, 12].Collection of ascitic fluid for laboratorial and microbiological analyses with every new paracentesis.Large-volume paracentesis will be performed as needed throught the ICU stay with a maximal duration of 8 h for each session.The volume of drained ascitis through LVP is determined by the attending physician, according to the usual clinical practice, without specified maximum volume limit.

#### Intervention group—continuous passive paracentesis

Ultrasound-guided (Ultrasound GE Vivid T8®) placement of an intra-abdominal double lumen catheter, Kit Certofix® Duo720, or similar, for paracentesis.Aseptic Seldinger technique, with an acute angle of percutaneous needle insertion.Adhesive, suture-free, abdominal wall catheter fixation.Continuous passive ascitic fluid drainage, preferentially through the proximal lumen (lateral opening) to minimize obstruction.Collection of ascitic fluid every 48 h for laboratorial and microbiological analyses.The trial intervention catheter will be in place for a maximum duration of 7 days.The catheter should be removed after 7 days of intervention or prior to ICU discharge, whatever occurs first.After the 7th day of intervention, paracentesis should be performed using the standard LVP approach as needed.

The 7-day duration of the intervention was determined based on previous studies revealing that the cumulative prevalence of IAH reaches a relative steady-state 5 days after ICU admission, with a median ICU stay of between 5 and 8 days in the studied populations [17, 18]. Furthermore, the impact of IAH on renal disfunction, assessed by the rise in serum creatinine, may lag up to approximately 3 days [19]. Therefore, we considered reasonable a period of 7 day for the trial intervention, while minimizing the risk of paracentesis catheter-associated infection, albeit considered safe [20–22].

### Criteria for discontinuing or modifying allocated interventions {11b}

The attending physician’s judgment is definitive regarding all clinical decisions, including protocol modification, interruption, or discontinuation, and these should be clearly stated in the patient’s clinical record.

In case of signs of catheter-related complication, particularly in the intervention group, appropriate therapeutic measures should be taken and the paracentesis catheter should be replaced when feasible at a different site for continued protocol intervention.

### Strategies to improve adherence to interventions {11c}

Strategies to improve adherence to the trial protocol include regular sessions and briefings with the nursing and medical staff throughout the duration of the trial addressing patient recruitment and enhanced protocol compliance, focusing on IAP and APP monitoring , 8 h urine sample collection procedures, and trial-related interventions.

### Relevant concomitant care permitted or prohibited during the trial {11d}

There are no restrictions to patient care during this trial.

#### Safety procedures and assessment

Clinical management will comply with current guidelines, including strict prevention, detection, and treatment of paracentesis-related complications, including paracentesis associated circulatory dysfunction, hypovolemia, intra-abdominal organ perforation and bleeding, catheter-related abdominal wall infection, and secondary peritonitis and abdominal wall fistula or bleeding [12]. Paracentesis-related complications and harm will be actively screened and reported by clinicians.

Paracentesis associated circulatory dysfunction is prevented with standard-of-care intravenous 20% albumin infusion (8 g for each 1 l of drained ascitic fluid) administered to all patients and, additionally, crystalloid infusion may be indicated by the attending physician to strictly avoid hypovolemia [12].

Intra-abdominal organ perforation and bleeding are prevented with (a) ultrasound guided paracentesis and (b) coagulopathy treatment, mandatory in case of severe thrombocytopenia (platelet count < 50,000/mL) or hypofibrinogenemia (< 0.7 g/L), as clinically indicated by the attending physician or the Blood Transfusion department [23–27].

Catheter-related abdominal wall infection and secondary peritonitis are to be prevented with aseptic paracentesis technique and standard catheter point of insertion surveillance for signs of inflammation or infection, similar to central venous catheter procedures [28].

We do not use prophylactic antibiotics along with the indwelling abdominal paracentesis catheter (IAPC) in the CPP intervention group nor in the control group.

The definition of secondary peritonitis includes the following: (1) polymorphonuclear cell count elevation > 50% in 48 h after the initial paracentesis or (2) microbiologic “de novo” isolation of bacteria after 48 h after paracentesis.

In case of isolated bacterial culture of suspected skin contaminants, without signs of infection, a new direct ascitic tap at a different site should be performed to confirm or exclude a diagnosis of secondary peritonitis.

Whenever a clinical diagnosis of secondary peritonitis is considered, then antibiotic treatment should be immediately started according to standard clinical practice.

In case of paracentesis catheter-associated infection in the intervention group, similar to catheter-related bloodstream infection diagnosis and treatment, the catheter must be removed and, when clinically feasible, replaced via a new direct ascitic tap at a different site [28]. This will allow for ascitic fluid analysis after 48 h to monitor for treatment response, according to clinical guidelines, and to complete the 7-day period of the trial intervention [12].

If abdominal wall fistula or bleeding occurs, the insertion point should be sutured for closure and hemostasis.

### Provisions for post-trial care {30}

The proposed interventions are to be, exclusively, implemented in the intensive care setting, although both post-trial care and patient follow-up will continue up to hospital discharge.

Patients enrolled in this study are covered from negligence or harm by the clinical trial insurance contracted by the study sponsor (CHULC, reference no. 706/22).

### Outcomes {12}

The primary outcome is serum creatinine concentration. The secondary outcomes are IAP, measured creatinine clearance, daily urine output, the multiorgan disfunction score Chronic Liver Failure Sequential Organ Failure Assessment (CLIF-SOFA) [13] and the incidence of stage 3 acute kidney injury (AKI) (defined by Kidney Disease: Improving Global Outcomes—KDIGO AKI [29] score), as well as 28-day renal replacement therapy (RRT)-free days, 28-day survival rate, and ICU LOS. The outcomes variables will be assessed at day seven (D7) after randomization (D0), unless otherwise stated. Additionally, IAP, serum creatinine concentration, measured creatinine clearance, daily urine output, and CLIF-SOFA will be analyzed using their maximum or minimum and daily mean values between D1 and D7.

Whenever ICU discharge or liver transplant occurs before D7, the last available data prior to these events will be used for outcome assessment. Additionally, stage 3 AKI will be considered when RRT or death occurs and, in these circumstances, a serum creatinine concentration value of 4 mg/dL and creatinine clearance value of 10 mL/min will be used for outcome assessment as mentioned in the literature [13, 29, 30].

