### Participant timeline {13}

The participants’ timeline begins with the screening for eligibility at ICU admission, obtainment of informed consent, enrolment, and randomized trial group allocation during the initial 24 h of stay. The calendar day in which group allocation takes place is considered trial “day zero” (D0).

The placement of the abdominal double-lumen catheter is intended to be performed as soon as possible after the allocation in the intervention group in order to optimize IAP and prevent and treat IAH. This procedure does not require special training beyond standard ultrasound-guided Seldinger technique.

Unforeseen catheter placement delay of more than 24 h after group allocation without clinical justification will lead to patient exclusion from the trial.

Protocol interventions and measurements will be maintained up to D7, after which post-trial care and follow-up will ensue until hospital discharge. This trial is expected to complete recruitment and follow-up of 70 patients in 36 months, until July 2025.

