## Statistical methods

### Statistical methods for primary and secondary outcomes {20a}

For the descriptive analysis, quantitative variables will be reported as means and standard deviations or as medians and interquartile ranges (*P*_25_-*P*_75_), as appropriate, and categorical variables reported as frequencies and percentages.

Quantitative variables will be analyzed using the assessment day value (D7), the daily mean value, and their maximum or minimum values. Mann–Whitney *U* test will be used to compare study groups, assuming a non-normal distribution, or two independent sample *t*-test, in case of normal distribution. Dichotomous categorical variables will be analyzed using chi-square or Fisher’s exact tests. Using daily values, mixed effects regression models will be used to consider the autocorrelation structure between the longitudinal measurements. Regarding stage 3 AKI as secondary outcome, odds ratios and corresponding 95% confidence intervals will be estimated using logistic regression models. For the study of RRT-free days, competing risks survival models will be applied considering death as the competing risk. Regarding time until death, joint survival regression models will be used to take into consideration the association of longitudinal markers with time until death. For LOS, linear regression models will be applied. For all regression studies, univariable and multivariable analyses will be performed to account for potential confounders. The absolute risk of paracentesis-related complications will be reported for both trial groups. A level of significance *α*= 0.05 will be considered. Data will be analyzed using the R Statistical Software [41].

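### The day-7 primary creatinine is replaced by the last ICU value after early ICU discharge, although a true day-7 value could be obtained for patients still in hospital

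*Protocol article*

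**What the plan says.** **Primary outcome.** Outcomes {12} names serum creatinine as primary and fixes the time: "The outcomes variables will be assessed at day seven (D7) after randomization (D0), unless otherwise stated". It then gives two substitution rules:

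- ICU discharge or transplant: "Whenever ICU discharge or liver transplant occurs before D7, the last available data prior to these events will be used for outcome assessment".
- RRT or death: "stage 3 AKI will be considered when RRT or death occurs and, in these circumstances, a serum creatinine concentration value of 4 mg/dL".

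Participant timeline {13} says that protocol measurements continue up to D7, and section {20c} says that missing data are described and not imputed.

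**Expected stay and lag.** The description of the intervention group justifies the 7-day period by earlier studies "with a median ICU stay of between 5 and 8 days in the studied populations". It adds that "the impact of IAH on renal disfunction, assessed by the rise in serum creatinine, may lag up to approximately 3 days".

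**Follow-up.** Provisions for post-trial care {30}: "both post-trial care and patient follow-up will continue up to hospital discharge". Participant timeline {13}: "post-trial care and follow-up will ensue until hospital discharge". Section {18b} likewise ties complete follow-up to the ICU and hospital stays. Yet Outcomes {12} lists 28-day survival and 28-day RRT-free days, and the auditing section {23} refers to patients who have completed 28 days of follow-up.

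**RRT-free days.** Section {20a}: "For the study of RRT-free days, competing risks survival models will be applied considering death as the competing risk".

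**The concern.** A day-7 endpoint is paired with a cited median ICU stay that straddles day 7, and measurement is tied to ICU presence. For a patient who leaves ICU alive before D7, the analysed value is the last ICU creatinine, even if the patient is on a ward of the same hospital on D7 and still followed.

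Two consequences follow. First, an earlier value may show less of the treatment effect, because the protocol itself expects creatinine to trail intra-abdominal pressure. Second, the time of measurement is set by a discharge decision made by staff who know the allocation. In the intervention arm the catheter is to be out before ICU discharge, so discharge timing could differ by arm; the direction is unknown.

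The two substitution rules also overlap for a patient who leaves ICU and then dies or starts RRT before D7. For the secondary outcomes, the stated end of follow-up and the 28-day horizon do not match, and the model named for RRT-free days answers a different question.

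**Working it through.** **1. The plan's own figure.** Inputs from Sample size {14}: difference 0.4 mg/dL, SDs 0.45 and 0.48, one-sided alpha 0.05, power 95%. Pooled SD = √((0.45² + 0.48²)/2) = 0.465. The noncentral t calculation gives 30 per arm, N = 60, power 0.950. The stated 60 reproduces.

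**2. Share of stays ending before day 7.** The median m = 5 or 8 days is from the protocol; the shape of the distribution is assumed. Conditioning on stays over 3 days stands in for the exclusion of predictably short stays (under 72 h).

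- Exponential, all stays: 1 − 2^(−7/m) = 62% (m = 5), 45% (m = 8).
- Exponential, stays over 3 days: 1 − 2^(−4/m) = 43%, 29%.
- Log-normal: F(t) = Φ(ln(t/m)/σ); for stays over 3 days the share is [F(7) − F(3)]/[1 − F(3)].

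| Stays over 3 days | m = 5 | m = 8 |
|---|---|---|
| Exponential | 43% | 29% |
| Log-normal, σ = 0.6 | 64% | 38% |
| Log-normal, σ = 0.8 | 54% | 36% |
| Log-normal, σ = 1.0 | 47% | 34% |

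The range is 29% to 64%; of 70 patients, 0.29 × 70 ≈ 20 to 0.64 × 70 ≈ 45. Allocation takes place within 24 h of admission, so D7 falls at about ICU day 7 to 8; evaluated at day 8, the top of the range is 73%. All these shares include stays that end in death and patients who received RRT. Both groups get 4 mg/dL, and the protocol gives no rate for either.

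**3. What carried-forward values could do to power.** Let a fraction f be carried forward and show a fraction e of the full effect. The expected difference is 0.4 × [(1 − f) + f·e]. With 30 per arm, one-sided 0.05 and the SD held at 0.465:

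| f | e | Difference (mg/dL) | Power |
|---|---|---|---|
| any | 1 | 0.40 | 0.950 |
| 0.3 | 0.5 | 0.34 | 0.875 |
| 0.5 | 0.5 | 0.30 | 0.795 |
| 0.5 | 0 | 0.20 | 0.50 |

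Both f and e are assumptions; the table illustrates the stakes and is not a forecast.

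**4. Overlap of the two rules.** Take a patient who leaves ICU on day 4 and dies on day 6. If the last ICU value was 1 to 2 mg/dL (assumed), choosing 4 instead changes that patient's value by 2 to 3 mg/dL. In an arm of 35 this moves the mean by 2/35 = 0.06 to 3/35 = 0.09 mg/dL, or 14% to 21% of the 0.4 mg/dL target.

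**5. Follow-up wording.** Sections {30}, {13} and {18b} run follow-up to hospital discharge. Outcomes {12} and section {23} need status at day 28. For a patient discharged home before day 28 both cannot describe the same procedure, and the article does not say how status is then obtained.

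**6. RRT-free days.** This is a count over 28 days. A competing-risks model with death as the competing event describes time to first RRT. Two survivors who start RRT on the same day, one for a short course and one through day 28, are identical in that model and far apart in the count.

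**The case against.** The strongest defence is that the intervention is delivered only in ICU, so a prespecified end-of-ICU value is a coherent choice. Creatinine is also to be analysed by its extreme and mean values over D1 to D7 and by mixed models on daily values, and those models do not need a carried-forward D7 value. This softens the point but does not remove it. D7 is the stated assessment time, the analysis is by intention to treat, and measurement need not stop when treatment stops.

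Several stronger readings are tempting, and the protocol does not support them:

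- **That a known, large share of primary values is carried forward.** The medians come from other populations, the stay distributions are assumed, and deaths and RRT cannot be netted out. The 20 to 45 patients are stays ending early, not carried-forward values.
- **That an ICU value from day 3 or 4 misses the effect.** The protocol says the lag may be up to about 3 days, which is an upper bound. Such a value may show less of the effect, or all of it.
- **That 28-day outcomes go unobserved after discharge.** Section {23} presupposes completed 28-day follow-up. The wording is inconsistent; a loss of data is not established, and the means of contact may stand in the full protocol.
- **That more early deaths would read as benefit for RRT.** This holds for a cumulative-incidence or subdistribution model, where early deaths lower RRT incidence. It need not hold for cause-specific hazards, and the type is not stated. Survival is reported alongside.

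On the overlapping rules, the order of the sentences suggests that the 4 mg/dL rule is meant to prevail. That is a natural reading, but precedence is not stated.

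**Conclusion.** The point holds as a badly fixed measurement rule for the primary outcome. The protocol ties the D7 creatinine to ICU presence although it follows patients to hospital discharge and says measurements continue to D7. A possibly substantial share of primary values is affected: 29% to 64% of stays over 3 days end before day 7 under the assumed distributions, less an unknown number of deaths and RRT patients. Any loss of power depends on how much of the effect earlier values show, and there is none if they show all of it. A bias from unblinded discharge timing is possible, with unknown direction and size. A reader might infer that the sample size is wrong; its arithmetic reproduces and is not in question here.

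Two secondary points also hold: the follow-up wording must be reconciled with the 28-day outcomes, and the competing-risks model does not match RRT-free days.

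**What to change.** **Primary outcome.** In Outcomes {12}, use the actual D7 creatinine for every patient still in hospital on D7, on the ward or in ICU. Carry a value forward only after hospital discharge or liver transplant. State that death or RRT by D7 takes precedence over carry-forward. Align the text with the statements that measurements run to D7 and that missing data are not imputed.

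**28-day outcomes.** Record vital status and RRT status at day 28 for all patients, by record check or telephone call, and amend sections {30}, {13} and {18b} to agree with {12} and {23}.

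**RRT-free days.** Analyse them as a count, with a prespecified score for death by day 28 (for example 0) and a rank test; the plan already names the Mann–Whitney test. Keep the competing-risks model for time to first RRT and state which type it is.

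**Cost.** One routine ward creatinine per patient discharged from ICU before D7, one record check or call per patient discharged from hospital before day 28, and wording.

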#### Patient eligibility

All patients with liver cirrhosis admitted in the ICU stay are eligible for this trial.

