#### Exclusion criteria

Exclusion criteria are defined by the following:Extreme age (≥ over 75 years old),Acute surgical condition or laparotomy in the preceding 4 weeks,Previous liver transplant,Hemorrhagic ascites (red blood cells count > 10,000/mL) [16],Extreme clinical severity (APACHE II ≥ 34),Any of the following conditions present 24 h after admission:aHemorrhagic shock with active uncontrolled bleeding,bRefractory shock (mean arterial pressure < 65 mmHg) despite multiple vasopressor support,Predictably short (< 72 h) ICU stay andTherapeutic futility determined by the medical staff.

Notes:These criteria are to be applied independently of any previous treatments of ascites, including recent LVP (i.e., in the emergency department before ICU admission), andExamples of “predictably short (< 72 h) ICU stay, precluding patient enrolment, may be, i.e., the reversal of clinical instability after initial therapy and adequate resuscitation in the ICU, such as < 6 h of vasopressor support; variceal bleeding controlled in the ICU without developing organ failure; or prompt reversal of oliguria/AKI.

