## Assignment of interventions: allocation

### Sequence generation {16a}

The patient allocation method consists of stratified randomization with blocks within each subgroup. This method is particularly useful with randomizing small samples due to the ability to create balanced groups regarding predetermined variables or characteristics at the beginning of the trial, reducing differences in baseline trial groups characteristics’ that could harm later result analysis and conclusions.

In this small sample size trial, patients will be stratified according to maximum serum creatinine and maximum IAP, expected to be the two most important variables to balance between trial groups at baseline. Stratified randomization will homogenize trial groups ad initio to reduce the probability of unbalanced baseline group characteristics and biased results.

The stratification process will use two strata, namely, maximum IAP and maximum serum creatinine, thus creating four subgroups (I–IV): (I) IAP < 16 mmHg + serum creatinine < 1.5 mg/dL, (II) IAP < 16 mmHg + serum creatinine ≥ 1.5 mg/dL, (III) IAP ≥ 16 mmHg + serum creatinine < 1.5 mg/dL, and (IV) IAP ≥ 16 mmHg + serum creatinine ≥ 1.5 mg/dL [4, 13]. Each subgroup (I–IV) contains sequential blocks of randomized trial group allocation (A) control and (B) intervention, with a 1:1 ratio (i.e., *AABB*, *ABAB*, *BABA*, *BBAA*), as exemplified in Table 1.

**Table 1 Tab1:** Stratification subgroups (I-IV) created using maximum intra-abdominal pressure (IAP) and serum creatinine as strata. Example of stratified randomization with blocks within each subgroup (A, B)

Stratification subgroups (I–IV)	Creatinine < 1.5 mg/dL	Creatinine ≥ 1.5 mg/dL
IAP < 16 mmHg	I) ABAB, ABBA,…	III) BABA, BBAA,…
IAP ≥ 16 mmHg	II) BABA, AABB,…	IV) BBAA, BAAB,…

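### Patients already on RRT before allocation can enter the trial, and the assigned-value rule can then set their day-7 creatinine, clearance and stage 3 AKI status whatever arm they are in

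*Protocol article*

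**What the plan says.** All places are in the protocol article.

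- **Patient eligibility:** "All patients with liver cirrhosis admitted in the ICU stay are eligible for this trial". The inclusion criteria add adult age and ascites of grade 2 or more, and no renal condition.
- **Exclusion criteria:** severity is limited by "Extreme clinical severity (APACHE II ≥ 34" and by refractory shock, active bleeding and futility. The only renal wording is "prompt reversal of oliguria/AKI", an example of a predictably short stay. RRT, chronic dialysis and persistent AKI are not excluded.
- **Sequence generation {16a}:** "patients will be stratified according to maximum serum creatinine and maximum IAP", cut at 1.5 mg/dL. The highest stratum is "IV) IAP ≥ 16 mmHg + serum creatinine ≥ 1.5 mg/dL", with no upper limit and no separate level for RRT.
- **Outcomes {12}:** "The primary outcome is serum creatinine concentration", assessed at D7. The assigned-value rule reads: "Additionally, stage 3 AKI will be considered when RRT or death occurs and, in these circumstances, a serum creatinine concentration value of 4 mg/dL"; clearance is set to 10 mL/min in the same sentence. A secondary outcome is "the incidence of stage 3 acute kidney injury (AKI"), with no restriction to patients free of stage 3 at baseline.
- **Participant timeline {13}:** allocation falls within the first 24 h of ICU stay, and D0 is the whole calendar day of allocation.

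**The concern.** Read together, the eligibility list and the scoring rule let an event that precedes randomisation determine the primary outcome. A patient on chronic dialysis, or one who starts acute RRT between ICU admission and allocation, is eligible. If RRT continues, the rule as worded gives 4 mg/dL, 10 mL/min and stage 3 AKI at D7 under either paracentesis strategy.

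Such patients pull both arms towards the same value, and their distance from the other patients inflates the variance. They can also fall unevenly between arms by chance, since a patient with creatinine 1.6 mg/dL and a dialysed patient share a stratum. This matters most at the interim analysis after 30 patients, where a significant primary difference stops the trial.

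Patients in stage 3 AKI without RRT at entry raise a narrower issue. An outcome called an incidence should count new events, but nothing removes patients who already had the event.

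**Working it through.** **1. Inputs (Sample size {14}).** Difference 0.4 mg/dL; means 0.9 and 1.3; SDs 0.45 and 0.48; one-sided alpha 0.05; power 95%; 60 patients, raised to 70 for about 15% attrition. The share p on RRT before allocation is not in the documents, so it is an assumption, varied from 5% to 30%.

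**2. The plan's own figure.** Pooled SD = sqrt((0.45² + 0.48²)/2) = 0.465. With 30 per arm the noncentrality is (0.4/0.465) × sqrt(30/2) = 3.33 on 58 degrees of freedom. One-sided power is 95.0%, so the stated 60 reproduces. Attrition: 60/0.85 = 71 and 60 × 1.15 = 69, consistent with 70. This calculation contains no patient fixed at 4 mg/dL.

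**3. Adding a share p fixed at 4 mg/dL in both arms.**
- Arm mean = (1 − p)m + 4p, so the difference is 0.4(1 − p).
- Arm variance = (1 − p)s² + p(1 − p)(4 − m)².
- Example, p = 0.10: 0.9 × 0.45² + 0.09 × 3.1² = 1.047 and 0.9 × 0.48² + 0.09 × 2.7² = 0.863. SD = sqrt((1.047 + 0.863)/2) = 0.98, and the difference is 0.36.

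Power at 30 per arm, one-sided 0.05 (noncentral t; Mann-Whitney by simulation):

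| p | Difference | SD | t-test | Mann-Whitney |
|---|---|---|---|---|
| 0 | 0.40 | 0.47 | 95% | 94% |
| 5% | 0.38 | 0.78 | 59% | 89% |
| 10% | 0.36 | 0.98 | 41% | 81% |
| 15% | 0.34 | 1.12 | 31% | 72% |
| 20% | 0.32 | 1.24 | 26% | 63% |
| 30% | 0.28 | 1.39 | 19% | 45% |

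Simulated t-test power agreed within about 2 percentage points. Most of the t-test loss comes from the variance rather than from the smaller difference.

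**4. Chance imbalance.** At the planning means, one such patient in place of an average one moves an arm of 35 by (4 − 1.3)/35 = 0.08 to (4 − 0.9)/35 = 0.09 mg/dL. At the interim, with about 15 per arm, the shift is 2.7/15 = 0.18 to 3.1/15 = 0.21 mg/dL, about half of the 0.4 target.

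**5. Stage 3 AKI odds ratio.** For illustration, assume new stage 3 AKI in 45% and 25% of patients at risk (not from the documents). The odds ratio is (0.45/0.55)/(0.25/0.75) = 2.45. Adding a share p who count as events regardless gives rates p + 0.45(1 − p) and p + 0.25(1 − p):
- p = 10%: 0.505 and 0.325, OR 2.12
- p = 20%: 0.56 and 0.40, OR 1.91
- p = 30%: 0.615 and 0.475, OR 1.77

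**The case against.** **The wording may mean new RRT only.** A rule triggered when RRT occurs, in a paragraph about a D7 assessment, can be read as covering events during follow-up. That reading is possible but not stated, and the text does not say what value applies if RRT stops before D7. In a trial where analysts are unblinded, the choice should not wait until data are seen.

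**The share may be small.** Allocation comes within 24 h of admission, and the sickest patients are excluded. Nothing in the documents shows that entry RRT is common, so every power figure above is conditional. Under the planned methods, clearly non-normal data go to the Mann-Whitney test, so its milder losses are the more relevant column.

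**Deaths and new RRT also produce values of 4 mg/dL.** This is true, and the fix leaves those in place. With them present, planning power would not be 95% to begin with, and the further loss from entry RRT would differ from the table.

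**Such patients may legitimately be enrolled, and the analysis is ITT.** They do inform IAP, survival and length of stay, so any restriction should be confined to the three renal outcomes. The creatinine subgroup and the multivariable models do not resolve the scoring. The exclusion list and the scoring rule are both stated in the article, so this is not merely detail left to an analysis plan.

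**Stronger readings that the documents do not support.** A reader might infer that patients in stage 3 AKI at entry also have their primary value fixed. They do not: without RRT or death the rule is not triggered, their D7 creatinine (or last value before discharge or transplant) is measured, and stage 3 is assessed at D7, so treatment can still change it. A reader might infer systematic bias, but randomisation balances entry RRT in expectation. A reader might also treat RRT on D0 as a baseline feature, but D0 includes hours after allocation.

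**Conclusion.** The point holds for patients whose RRT, chronic or acute, began before allocation. They are eligible, the rule as worded can score them identically in either arm, and the stratification does not balance them. While RRT continues they contribute nothing to the comparison of creatinine, clearance or stage 3 AKI. For stage 3 AKI without RRT at entry, the only defect is that incidence is not limited to patients at risk.

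The size rests on an unknown share. At 5-20% per arm, with all other patients at the planning means and SDs and none fixed at 4 mg/dL for another reason, power falls from 95% to 59-26% (t-test) or 89-63% (Mann-Whitney). If no such patient is enrolled, the loss is nil.

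**What to change.** 1. Add RRT, chronic or acute, before the time of allocation to the exclusion criteria for further enrolment.
2. For patients already enrolled, leave out of the creatinine, clearance and stage 3 AKI analyses only those whose RRT began before the time of allocation. Report them separately and keep them in all other ITT outcomes. Do not define the restriction by RRT on D0: RRT started later that day is post-randomisation, and excluding on it in an open-label trial could introduce bias.
3. Add a sensitivity analysis of all randomised patients under the scoring as now worded.
4. Limit the assigned values to RRT started after allocation, and state which value is used when RRT stops before D7.
5. Analyse stage 3 AKI as new onset among patients not in stage 3 at their last assessment before allocation.

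The cost is a short amendment, best made before the interim analysis, with slightly slower recruitment and a few patients fewer in the renal analyses. KDIGO variables and days on RRT are already collected, and creatinine is needed before allocation for stratification. The start time of RRT relative to allocation has to be taken from the clinical record.
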